### Imaging endpoints

After completion of patient enrollment, all imaging data will be evaluated by the core imaging laboratory. Stroke neurologists, neuroradiologists, and neurointerventionists with expertise in acute stroke management will perform core laboratory imaging analyses to ensure consistent grading and eliminate possible bias after de-identification and blinding of clinical data. The core laboratory team will assess the ASPECTS, infarct volume, recanalization defined by modified Thrombolysis in Cerebral Infarction grades, and the presence of hemorrhagic transformation. All core laboratory readings will be performed independently by two experienced readers. Discrepancies will be resolved by a third, independent reader.

### Sample size estimates

The primary hypothesis of this study is that patients receiving Neu2000 before EVT will have an increased proportion of 3-month functional independence (mRS 0–2), compared with those receiving placebo. The expected proportions of functional independence are 41.6% and 70.0% in the placebo and Neu2000 groups, respectively. Such assumptions are based on the results of CT-based EVT trials (MR CLEAN [17] and ESCAPE [18]), and the preclinical Neu2000 research with transient occlusion model [9]. We chose the target sample size of 63 participants per group to provide 90% power, at a two-sided alpha of 0.05 to prove a treatment effect. The total sample size was determined to be 210 considering a 10% dropout rate for the primary endpoint.

### Statistical analyses

The primary outcome analysis is based on the intention-to-treat principle. Statistical testing for the primary endpoint is conducted using the chi-square test for the comparison of functional independence among the three arms at a two-sided significance threshold of 10%. In case of significant differences, comparisons between the placebo and low-dose Neu2000 groups, and placebo and high-dose Neu2000 groups will be conducted. For secondary outcome analyses, the Cochran-Mantel-Haenszel test, the two-way analysis of variance test, and the chi-square test will be performed on the per-protocol population. In addition, multivariate analysis will be used to adjust for potential confounders, such as age, stroke severity, time to EVT onset, previous stroke, atrial fibrillation, diabetes mellitus, ASPECTS, and T-type internal carotid artery occlusion. If there are missing data despite best efforts to keep all missing data to a minimum, then missing outcome data will be not substituted for the primary outcome analysis.

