### Treatment

A study subject is enrolled after clinical judgment with inclusion and exclusion criteria on the basis of acute-onset neurological manifestation, confirmed by imaging for arterial vessel occlusion. Written informed consent is obtained from the patient or a legal representative before enrollment. After enrollment, the study subject undergoes rapid endovascular recanalization therapy. The neuro-interventionist uses any available modality (stent retriever or aspiration thrombectomy) or its combination to achieve safe recanalization. In addition, the use of a balloon-guided catheter is recommended in the relevant internal carotid artery. All groups will receive the best current standard of care as described in the current local guidelines for acute stroke management: This represents the fact that they will receive tissue plasminogen activator intravenously in a 4.5-h window if they meet the accepted criteria [15].

The assigned groups are injected with intravenous administration of IP as a high-dose, low-dose, or placebo of Neu2000KWL (2-hydroxy-5-(2,3,5,6-tetrafluoro-4-trifluoromethyl-benzylamino)-benzoic acid) before recanalization attempt by the personnel who are blinded to treatment allocation. The first infusion is intended to be initiated before thrombus retrieval. Subsequent injection will be administered twice per day (12-h interval) during five consecutive days. In the high-dose group, the initial infusion dose is 750 mg mixed with 250 mL of saline; the subsequent nine doses are 500 mg (total dose: 5250 mg). In the low-dose group, the initial infusion dose is 500 mg, and the subsequent nine doses are 250 mg (total dose: 2750 mg). The placebo group receives 250 mL of saline 10 times. The infusion volume is 250 mL in all groups. All patients receive care in the stroke unit or neuro intensive care unit. Follow-up imaging studies will be obtained as computed tomography (CT) angiography at 24–48 h from the first infusion and subsequent magnetic resonance imaging within 24 h from the last infusion. Follow-up images play a role in the detection of adverse effects of the study drug.

All patients visit at the fourth week and third month after randomization. During follow-up, modified Rankin Scale (mRS) score, NIHSS score, and Barthel Index (BI) will be determined. Adverse events are collected throughout the study. Detailed follow-up schedules and procedures are shown in Fig. 3.

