### Study outcome

The primary outcome will be assessed by a dichotomous model: the proportion of patients with mRS 0–2 and that with mRS 3–6 at 3 months. Safety outcomes are all serious adverse events and symptomatic intracranial hemorrhage with neurologic deterioration (NIHSS score ≥ 4) on cerebral CT within 24–48 h after randomization [16]. The secondary outcomes are as follows: distributional change of mRS, difference in NIHSS score, ratio of NIHSS score 0–2, and ratio of BI ≥ 90 at 1, 4 weeks, and 3 months. All local principal investigators (PI) have a consensus meeting for imaging interpretation before the start of the trial and present regular meeting bi-annually.

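### The deciding test is an unadjusted three-arm chi-square; adjusting it for age, baseline NIHSS and ASPECTS would gain a modest amount of power and robustness at almost no cost

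*Protocol article*

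**What the plan says.** The primary endpoint (Study outcome) is binary: "the proportion of patients with mRS 0–2 and that with mRS 3–6 at 3 months". The Statistical analyses section fixes the test: "Statistical testing for the primary endpoint is conducted using the chi-square test", applied to all three arms at once. The level of this test is set "at a two-sided significance threshold of 10" per cent. If it is significant, "comparisons between the placebo and low-dose Neu2000 groups, and placebo and high-dose Neu2000 groups will be conducted". No covariate enters at either step.

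After the secondary analyses, the same section adds a multivariate analysis to "adjust for potential confounders, such as age, stroke severity, time to EVT onset". The list goes on to ASPECTS, earlier stroke, diabetes, atrial fibrillation and T-type carotid occlusion. The section does not make that analysis the deciding one.

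Table 1 makes age, NIHSS at screening and ASPECTS eligibility criteria, and the Patient population section has ASPECTS assessed before randomisation. The sample size was chosen "to provide 90% power, at a two-sided alpha of 0.05 to prove a treatment effect", from an unadjusted comparison of 41.6% with 70.0%.

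**The concern.** The plan regards age, severity and ASPECTS as prognostic enough to adjust for, and it has all three for every eligible patient before allocation. The test that decides the trial does not use them. Two things are at stake.

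- **Power.** For a binary outcome, adjusting for prognostic baselines usually raises the power of the arm comparison with no extra patients.
- **Chance imbalance.** With about 63 evaluable patients per arm, two arms can differ by chance on a prognostic score. An unadjusted test leaves that difference in the result. If the adjusted and unadjusted analyses then disagree, the reading is open to dispute.

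**Working it through.** **1. The plan's own figure.** Inputs from Sample size estimates: p1 = 0.416, p2 = 0.700, two-sided alpha 0.05, power 0.90. With the pooled variance and no continuity correction:

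n = [z(0.975)·√(2·p̄·(1−p̄)) + z(0.90)·√(p1(1−p1) + p2(1−p2))]² / (p2−p1)²

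- p̄ = (0.416 + 0.700)/2 = 0.558. First term: 1.960 × √0.4933 = 1.3765.
- Second term: 1.2816 × √(0.2429 + 0.2100) = 1.2816 × 0.6730 = 0.8625.
- n = (2.2390)² / (0.284)² = 5.0133 / 0.08066 = 62.2, so 63 per arm.
- Dropout: 63/0.90 = 70, and 3 × 70 = 210. All three stated figures reproduce.
- Power at 63: Φ[(0.284 × √63 − 1.3765)/0.6730] = Φ(1.304) = 90.4%.

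The plan meets its target without adjustment.

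**2. Power of the test that actually decides.** This is the three-arm chi-square at 10%. With 63 per arm and rates 41.6/70/70%, the mean rate is 0.6053 and the noncentrality is 63 × [(0.1893)² + 2 × (0.0947)²] / (0.6053 × 0.3947) = 14.2. On 2 degrees of freedom, with critical value 4.605, the power is about 96.4%. Little headroom is left at the design effect.

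**3. Adjusted test with three covariates.** The documents do not say how well the covariates predict mRS 0–2, so the AUC is assumed over a range. The simulation used 63 per arm and 3,000 trials per setting. It compared the chi-square with a logistic likelihood-ratio test for arm, with three estimated covariates and nominal critical values. Entries are unadjusted then adjusted power.

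| Assumed AUC | Three-arm at 10%, 41.6/70/70% | Pairwise at 5%, 41.6 vs 70% | Three-arm at 10%, 41.6/60/60% (assumed) |
|---|---|---|---|
| 0.70 | 95.9 → 97.5% | 90.9 → 92.3% | 69 → 73% |
| 0.77 | 96.4 → 98.7% | 91.5 → 95.4% | 70 → 79% |
| 0.81 | 96.0 → 99.3% | 91.3 → 97.0% | 70 → 82% |

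The gains are about 1 to 3 points, 1 to 6 points and 4 to 12 points. Simulation error is about √(0.7 × 0.3/3000) = 0.8 point at 70% power, and less near 96%. Under the null, the three-arm rejection rate at nominal 10% was 11.2–11.6% adjusted against 10.5–11.1% unadjusted, so little of the gain is bought with type I error.

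**4. Sensitivity: eight covariates.** With as many covariates as the plan lists, the raw adjusted three-arm test was slightly liberal (about 0.11–0.12 at nominal 0.10). After recalibrating it to nominal size, for AUC 0.70/0.77/0.825:

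- Three-arm at the design effect: 96.6 → 97.4%, 96.7 → 98.5%, 96.7 → 99.2%.
- Pairwise at the design effect: 91.4 → 91.0%, 91.2 → 94.2%, 91.8 → 96.5%.

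At AUC 0.70 the long list gains nothing pairwise. That argues for a short list.

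**5. Chance imbalance.** Under simple allocation, the chance that two arms of 63 differ by more than 0.25 SD on the prognostic score is 2 × [1 − Φ(0.25/√(2/63))] = 2 × [1 − Φ(1.40)], about 16%. In those trials the simulated type I error of the unadjusted pairwise test at 5% was about 7%, 12% and 14% (AUC 0.70, 0.77, 0.825), against 4–5% adjusted.

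**The case against.** The strongest reply is that nothing here is wrong. A chi-square test is valid under randomisation, the sample size was built for an unadjusted comparison and reproduces, and adjustment is already planned. All of this stands, and it is why the point is one of efficiency and robustness.

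The gain also rests on an AUC that the documents do not supply. Entry criteria (NIHSS of at least 8, ASPECTS of at least 6, good prestroke function, at least moderate collaterals) narrow the spread of prognosis. The low end of the range is therefore plausible, and there the gain at the design effect is only 1 to 2 points. This stands too.

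Four stronger readings are tempting, and the documents do not support them.

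- **That the unadjusted test inflates type I error.** The 7–14% figures apply only to trials that happen to be imbalanced. Over all trials the error is near nominal.
- **That randomisation is unstratified.** The Randomization section names no factor, but a condensed article does not show that none exists. The 16% is for simple allocation; stratifying on these variables would lower it.
- **That the open covariate list is a defect.** Such detail is commonly left to the SAP, which is not shown.
- **That time to EVT onset is an invalid covariate because it follows the first infusion.** The Treatment section says "After enrollment, the study subject undergoes rapid endovascular recanalization therapy", and that the infusion is given before the recanalisation attempt and is meant to start before thrombus retrieval. It does not place the start of EVT after the first infusion, and the double blind leaves little route for allocation to affect that time.

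**Conclusion.** The point holds as a recommended improvement. The plan fixes an unadjusted deciding test although three prognostic baselines are available at no cost, and it names the same three factors for adjustment elsewhere. At the design effect the benefit is small, because the three-arm test at 10% already has about 96% power. It becomes worthwhile if the true effect falls short of the assumed 28.4 points: at a 60% rate on drug, unadjusted power is about 70% and adjustment recovers about 4 to 12 points.

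These sizes depend on the assumed AUC of about 0.70 to 0.81, 63 evaluable patients per arm, both doses having the same rate, and a correctly specified logistic model. The difference between the 5% level used for the sample size and the 10% level of the test is a separate matter and does not affect this conclusion.

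**What to change.** Before unblinding, reword the primary analysis in the Statistical analyses section:

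- Primary test: logistic regression of mRS 0–2 at 3 months on arm, adjusted for age, baseline NIHSS and ASPECTS, with this list fixed.
- Keep the existing order: first the joint three-arm test of arm, then each dose against placebo from the same kind of model if the joint test is significant.
- Report the standardised (covariate-averaged) difference in proportions for each dose against placebo with its confidence interval. The result then stays on the scale used for the sample size.
- Keep the chi-square test as a supportive analysis, and leave the wider covariate set to the added multivariate analysis.

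The change is to statistical wording only and needs no new patients or data. The price is a model-based p-value in place of a simple one. It can be slightly liberal in small samples, which is the reason to hold the list at three.

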### Randomization

Participants will be randomly assigned in a 1:1:1 fashion to one of three arms: (1) high-dose, (2) low-dose, or (3) placebo. Randomization is based on computer-generated cards before study initiation and will be handed to authorized personnel in a sealed envelope. All study investigators and participants are masked to treatment allocation except investigational product (IP)-preparing personnel. The randomization schedule is not accessible except for safety reasons, until completion of this trial. Study drugs and the placebo are provided in an identical package.

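### Secondary efficacy outcomes are tested only on an undefined per-protocol population, which can bias the comparisons with placebo

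*Protocol article*

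**What the plan says.** In the protocol article, Statistical analyses, the two tiers of outcome are placed on different sets. For the primary outcome: "The primary outcome analysis is based on the intention-to-treat principle". For the secondary outcomes: "the Cochran-Mantel-Haenszel test, the two-way analysis of variance test, and the chi-square test will be performed on the per-protocol population". No intention-to-treat analysis of the secondary outcomes is stated anywhere in the article, and no reason is given for the difference.

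The section Study outcome shows what is affected: "The secondary outcomes are as follows: distributional change of mRS, difference in NIHSS score", followed by the proportion with NIHSS 0–2 and the proportion with Barthel Index (BI) of at least 90. They are assessed at 1 week, 4 weeks and 3 months. All of them are efficacy outcomes.

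The section Treatment gives the course that a patient would have to complete. There is a first infusion around the thrombectomy, then nine more: "Subsequent injection will be administered twice per day (12-h interval) during five consecutive days".

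**The concern.** The trial compares two doses with placebo for superiority, and randomisation ("Participants will be randomly assigned in a 1:1:1 fashion to one of three arms") is what makes the arms comparable. A per-protocol set, as the term is normally used, is formed after randomisation and drops patients who did not receive the planned treatment. Entry requires an NIHSS of at least 8 and a large-artery occlusion. Patients who die, bleed, deteriorate or have an adverse event during the five dosing days are the ones least likely to receive all ten infusions. If they leave the set, exclusion is tied to poor outcome. If the drug affects how often this happens, it is also tied to arm.

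Two things are at stake. First, a difference in NIHSS, BI or mRS distribution could reflect who was removed and not what the drug did. Second, the mRS distribution at 3 months is the natural companion to the dichotomised mRS at 3 months, yet the two would be computed in different patients. Agreement or disagreement between them would then be hard to interpret. The usual reason for giving weight to a per-protocol set, in a non-inferiority comparison, does not apply here.

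**Working it through.** **The plan's own figure.** Inputs from Sample size estimates: "The expected proportions of functional independence are 41.6% and 70.0% in the placebo and Neu2000 groups, respectively"; "63 participants per group to provide 90% power, at a two-sided alpha of 0.05"; "The total sample size was determined to be 210 considering a 10% dropout rate for the primary endpoint". With a pooled variance and no continuity correction, the mean rate is (0.416 + 0.700)/2 = 0.558, and

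n = [1.960 × √(2 × 0.558 × 0.442) + 1.282 × √(0.416 × 0.584 + 0.700 × 0.300)]² / 0.284² ≈ 62.2, so 63 per group.

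Then 63/0.90 = 70 per group and 3 × 70 = 210. The stated sample size reproduces (power 90.4% at 63 per group). The point does not depend on it, and the fix does not change it.

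**Illustration of the possible bias.** The article gives no exclusion rates, so these are assumptions:
- no drug effect, with a true success rate of 41.6% in both arms. This is the placebo rate for mRS 0–2, borrowed as a stand-in because the article gives no rate for any affected secondary outcome;
- 70 patients per arm, and a pooled two-sided test at a nominal 5% (the article states no level for the secondary tests);
- a fraction e of an arm is excluded, and a fraction q of those excluded would have had a good outcome, with q = 0 or 0.20.

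The success rate among those analysed is (0.416 − e × q)/(1 − e).

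15% of the active arm and 5% of placebo excluded:
- q = 0: 0.416/0.85 = 48.9% vs 0.416/0.95 = 43.8%, a false benefit of 5.2 points.
- q = 0.20: (0.416 − 0.030)/0.85 = 45.4% vs (0.416 − 0.010)/0.95 = 42.7%, a false benefit of 2.7 points.

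10% vs 5% excluded:
- q = 0: 0.416/0.90 = 46.2% vs 43.8%, or 2.4 points.
- q = 0.20: (0.416 − 0.020)/0.90 = 44.0% vs 42.7%, or 1.3 points.

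Equal exclusion rates with equal q: 0 points.

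**Type I error.** With d the false difference and SE its pooled standard error, the two-sided error is approximately 1 − Φ(1.960 − d/SE) + Φ(−1.960 − d/SE). For 15% vs 5% and q = 0:
- the analysed numbers are 70 × 0.85 = 59.5 and 70 × 0.95 = 66.5, and the pooled rate is 0.462;
- SE = √[0.462 × 0.538 × (1/59.5 + 1/66.5)] = 0.089, so d/SE = 0.0515/0.089 ≈ 0.58;
- the error is about 8.9% (about 9.1% by simulation), nearly all of it favouring the drug.

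The other cases by the same formula: 6.1% for 15% vs 5% with q = 0.20; 5.9% and 5.2% for 10% vs 5% with q = 0 and 0.20; and 5.0% when exclusions are equal.

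The direction is not fixed. If placebo lost more poor-outcome patients than the active arm, the signs would reverse and a real benefit could be understated.

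**The case against.** The strongest reply has five parts.

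- **The set is undefined in the article.** The definition may properly sit in the full protocol or the analysis plan, and it might rest mainly on eligibility or on receiving the first infusion. This stands as a limit on wording. A reader might infer that the plan does remove patients because they died or bled, and so does bias the comparisons. The text does not establish that. It supports only that the comparisons can be biased under the usual meaning of the term. Naming per-protocol as the only set is nevertheless a stated rule, not a detail left out.
- **The illustration uses a borrowed rate and unfavourable exclusions.** This also stands. The 41.6% belongs to the primary outcome, which is not analysed per protocol, and the unequal exclusion rates are assumed. The 9% error is not a forecast.
- **Blinding limits selective exclusion.** Patients, treating physicians and assessors are masked. That restrains judgement-driven exclusion, but not exclusion that follows from effects of the drug itself.
- **The main readouts are protected.** A reader might infer that a harmful dose could pass as beneficial in the trial as a whole. The documents do not support this. The primary analysis is by intention to treat and counts death within mRS 3–6. Serious adverse events and symptomatic haemorrhage are separate safety outcomes that are not assigned to the per-protocol set. This is a phase-II proof-of-concept trial, and the affected outcomes are supportive. That lowers the severity.
- **Analysing everyone as randomised does not by itself settle NIHSS and BI in patients who die.** This is correct. The article's missing-data rule covers only the primary outcome, so the change needs a rule for deaths.

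**Conclusion.** The concern holds in a limited form. The article places every secondary efficacy outcome on a per-protocol set alone, while the primary outcome is by intention to treat. That choice can bias the secondary comparisons with placebo, and it separates the mRS shift from the dichotomised mRS it supports.

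Under the stated assumptions, excluding 15% vs 5% gives a false benefit of 2.7 to 5.2 points with about 6–9% type I error. Excluding 10% vs 5% gives 1.3 to 2.4 points with about 5–6%, and equal exclusion with equal prognosis gives none. The actual size and direction depend on a definition and on exclusion rates by arm that the article does not give.

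This is a should-fix matter: the primary analysis, the safety outcomes and the sample size are unaffected.

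**What to change.** In Statistical analyses, replace the per-protocol statement for the secondary outcomes with the following:
- Analyse all secondary efficacy outcomes in all randomised patients, in the arm to which they were randomised.
- Count deaths as failures in the NIHSS 0–2 and BI ≥ 90 responder analyses, and give deaths the worst rank or score in the NIHSS difference. The mRS distribution already has a category for death.
- Keep the per-protocol analyses as labelled sensitivity analyses.

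The cost is a short rewording and a second set of tables. Estimates may be slightly diluted by patients who did not complete treatment. The sample size stays at 210. The visits at 4 weeks and 3 months are already planned for all patients, so none need be added.

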**Methods:**

This trial is a phase-II, multicenter, three-arm, randomized, double-blinded, placebo-controlled, blinded-endpoint drug trial that enrolled participants aged ≥ 19 years undergoing an EVT attempt less than 8 h from symptom onset, with baseline National Institutes of Health Stroke Scale (NIHSS) score ≥ 8, Alberta Stroke Program Early CT score ≥ 6, evidence of large-artery occlusion, and at least moderate collaterals on computed tomography angiography. EVT-attempted patients are randomized into control, low-dose (2.75 g), and high-dose (5.25 g) Neu2000KWL over 5 days. Seventy participants per group are enrolled for 90% power, assuming that the treatment group has a 28.4% higher proportion of participants with functional independence than the placebo group. The primary outcome, based on intention-to-treat criteria is the improvement of modified Rankin Scale (mRS) scores at 3 months using a dichotomized model. Safety outcomes include symptomatic intracranial hemorrhage within 5 days. Secondary outcomes are distributional change of mRS, mean differences in NIHSS score, proportion of NIHSS score 0–2, and Barthel Index > 90 at 1 and 4 weeks, and 3 months.

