### Patient population

We will enroll acute ischemic stroke patients with moderate to severe neurological deficits (at least National Institutes of Health Stroke Scale (NIHSS) score ≥ 8) and imaging confirmation of proximal vessel occlusion in the anterior circulation. Before randomization, local investigators will assess imaging criteria with the Alberta Stroke Program Early CT Score (ASPECTS), definite proximal artery occlusion, and collateral status on baseline computed tomography (CT) and CT angiography (Fig. 2). Detailed study inclusion and exclusion criteria are shown in Table 1.

**Table 1 Tab1:** Study inclusion and exclusion criteria

Inclusion criteria	
1. Age ≥ 19 years	
2. Subject who is presented to hospitals after onset of brain ischemic symptoms from the base of last normal state and can start endovascular therapy in accordance with standard practice guidelines within 8 h after the symptom onset	
3. NIHSS ≥8 at screening time point	
4. Subject whose activity is possible without the help of others in the general condition 1 day before the ischemic stroke onset and prestroke Barthel Index scores > 90	
5. Subject whose cerebral CT and CTA imaging confirm acute ischemic stroke and symptomatic intracranial occlusion at screening and whose occlusion site considered the cause of acute ischemic stroke meets the following conditions: T- or L-type ICA occlusion, MCA M1 occlusion, MCA-M1 equivalent (2 or more MCA-M2, anterior temporal artery is not regarded M2)	
6. Subject with ASPECTS ≥ 6 on cerebral non-contrast CT	
7. Subject who spontaneously submit a written informed consent to participate in this trial	
Clinical exclusion criteria	
1. A medical history of hypersensitivity against aspirin (salicylates), sulfasalazine, or 5-ASA	
2. Subject whose heart diseases were confirmed at screening: Subject who was diagnosed with myocardial infarction within 6 months; subject who had severe arrhythmia evoking clinical symptoms (respiratory difficulties, tachycardia, etc.) within 6 months; subject whose ECG measured at the emergency room confirms the following results: A. pulse rate < 50 or > 120 beats/min. B. 2nd or 3rd degree AV block. C. congenital or acquired QT syndrome. D. ventricular pre-excitation syndrome	

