### Blinding

Treatment assignment will remain blind in both the patient and treating physician except IP-preparing personnel. The IP-preparing personnel are not involved in any other aspect of the study. Study outcomes at baseline, day 7, the fourth week, and third month will be assessed with standardized forms and procedures by separate certified investigators blinded to the treatment. Finally, the Blinded-endpoint Monitoring Board will determine the primary endpoint through central adjudication. Results of neuroimaging will also be assessed by the imaging core laboratory team who are unaware of the treatment allocation.

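### The two-way ANOVA that appears to serve the NIHSS score difference names neither baseline NIHSS as a covariate nor within-patient correlation; a baseline-adjusted model should be the main analysis

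*Protocol article*

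**What the plan says.** All statements are in the protocol article.

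- **Outcome.** The Study outcome section lists "difference in NIHSS score, ratio of NIHSS score 0–2, and ratio of BI ≥ 90 at 1, 4 weeks, and 3 months", besides a comparison of how mRS grades are spread. The abstract words the NIHSS item as "mean differences in NIHSS score".
- **Tests.** For the secondary outcomes, the Statistical analyses section names "the two-way analysis of variance test" beside a Cochran-Mantel-Haenszel and a chi-square test, all three in the per-protocol population. Tests are not paired with outcomes, and the two ANOVA factors are not named.
- **Baseline.** Table 1 requires "NIHSS ≥8 at screening time point", and the Blinding section says "Study outcomes at baseline, day 7, the fourth week, and third month will be assessed". A pre-treatment NIHSS should therefore exist for every randomised patient.
- **Covariates.** Statistical analyses adds that "multivariate analysis will be used to adjust for potential confounders, such as age, stroke severity, time to EVT onset" and further baseline factors. It does not say for which outcomes.
- **Deaths.** The article gives no rule for NIHSS after death. Its rule against substituting missing data is stated for the primary outcome only.

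**The concern.** The data are a score with a known starting value and three later readings in the same patient. A classical two-way ANOVA has two categorical factors. As named, it has no place for a continuous baseline covariate and no term for the correlation between a patient's readings. This is a named method that fits the data poorly, so it is more than a detail left for later.

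Precision is at stake. The trial plans 63 evaluable patients per arm, and the NIHSS difference is one of its supporting efficacy signals. Leaving baseline out of the main analysis gives up information that has already been collected. A mean NIHSS also has no natural value for a patient who has died, whereas the mRS scale used for the primary outcome runs to 6 and keeps deaths in the comparison.

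**Working it through.** **1. The plan's own figure.** With 41.6% against 70.0%, two-sided alpha 0.05 and 90% power, the pooled-variance formula without continuity correction is

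n = [1.960·√(2·0.558·0.442) + 1.282·√(0.416·0.584 + 0.70·0.30)]² / 0.284² ≈ 62.2, rounded up to 63.

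Then 63/0.9 = 70 per arm and 3 × 70 = 210. The sample size reproduces. It concerns the binary primary outcome; the article gives no SD, correlation or power for NIHSS, so every correlation below is an assumption.

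**2. Which outcome the ANOVA serves.** The mRS distribution is ordinal. NIHSS 0–2 and the Barthel Index threshold are proportions. The NIHSS score difference is the only item left for an ANOVA. This is an inference, but no other listed secondary outcome fits.

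**3. Precision.** Let r be the correlation between baseline and follow-up NIHSS, with equal variances at both times. Relative to raw follow-up scores (variance 1):

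- change score: 2 − 2r
- ANCOVA on baseline: 1 − r²
- ANCOVA relative to change score: (1 − r²)/(2 − 2r) = (1 + r)/2

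| Assumed r | ANCOVA vs raw | Reduction | 63 per arm acts like | ANCOVA vs change | Reduction |
|---|---|---|---|---|---|
| 0.4 | 0.84 | 16% | 63/0.84 = 75 | 0.70 | 30% |
| 0.5 | 0.75 | 25% | 63/0.75 = 84 | 0.75 | 25% |
| 0.6 | 0.64 | 36% | 63/0.64 ≈ 98 | 0.80 | 20% |

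Over a wider range of r, 0.3 to 0.7, the reduction against raw scores runs from 9% to 49%. ANCOVA gains whether the outcome is the follow-up score or the change from baseline.

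**4. Type I error, under one reading only.** Suppose the factors are arm and visit and the three visits are treated as independent. With within-patient correlation ρ, the true variance of an arm mean over visits is 1 + 2ρ times the assumed one. The standard error is then too small by a factor √(1 + 2ρ). A large-sample approximation for the three-arm test at nominal 5% is P(χ² on 2 df > 5.99/(1 + 2ρ)) = exp[−5.99/(2(1 + 2ρ))]. The simulation used 3 arms × 63 patients × 3 visits, equal correlation between visits and 4,000 runs.

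| Assumed ρ | √(1 + 2ρ) | Approximation | Simulated, arm effect | Simulated, arm-by-visit |
|---|---|---|---|---|
| 0.3 | 1.26 | 15% | 16% | 0.8% |
| 0.5 | 1.41 | 22% | 23% | 0.2% |
| 0.7 | 1.55 | 29% | 30% | 0.0% |

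Testing each patient's mean over visits, so that the patient is the unit, held the error at about 5% throughout. Under the same faulty reading, the interaction test errs in the opposite direction and is conservative.

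**The case against.** Three stronger readings are tempting, and the article supports none of them.

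- **That baseline NIHSS goes unused.** The text does not say so. The NIHSS difference may mean change from baseline, and the multivariate sentence adjusts for stroke severity, which in this trial is naturally the baseline NIHSS. That sentence directly follows the one on secondary outcomes. It remains additional, however, names no outcome, and does not say which result takes precedence. A change score is also less precise than ANCOVA for any r below 1 under equal variances.
- **That the standard errors are wrong.** This needs arm and visit as the factors, independent errors, and an arm effect pooled over visits. None of these is stated. The second factor could be something else, or the ANOVA could be run per visit or in a repeated-measures form. The outcome is defined at each visit, and the arms hold different patients, so an arm contrast at one visit keeps its usual standard error (given similar variances) whatever the within-patient correlation.
- **That the means compare survivors only.** The article is silent on NIHSS after death, and silence is not a rule.

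It is also fair that factors, covariance structure and death handling for a secondary outcome are commonly left to a full protocol or SAP, so their absence from an article is not a fault. What remains is that the article does name a method, and the method as named is a weak choice for these data.

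**Conclusion.** The point holds in a limited form. The test that by inference serves the NIHSS score difference is ambiguous and, as named, carries neither baseline NIHSS nor within-patient correlation. The additional multivariate analysis softens this without replacing the listed test.

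The likely cost is precision: variance 16% to 36% higher than it need be as a share of the raw-score variance, or 30% to 20% as a share of the change-score variance, for assumed r of 0.4 to 0.6. The change-score comparison also assumes equal variances at baseline and follow-up. The type I error of 16% to 30% (assumed ρ of 0.3 to 0.7) is a conditional risk of one possible reading and should not be reported as a defect of the plan. Validity is therefore not shown to be compromised. This is a worthwhile correction to a secondary analysis.

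**What to change.** Replace the two-way ANOVA for NIHSS with one of the following as the main analysis:

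- an ANCOVA at each visit, with arm and baseline NIHSS; or
- a mixed model for repeated measures, with arm, visit, arm-by-visit interaction, baseline NIHSS and within-patient correlation.

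State which outcomes the additional multivariate analysis covers and that it supports the main NIHSS analysis.

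For deaths, a supporting rank-based analysis that places deaths worst can be shown beside the adjusted means. It answers a somewhat different question from the mean difference, combining survival with neurological score, so it should be labelled as supporting.

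The cost is a few lines of text and standard software, with no new data, visits or patients. The rank analysis is harder to express in NIHSS points, which is why the adjusted means should stay alongside. The wording should be settled before unblinding.
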